## Abstract

**Background:**

Despite the importance and popularity of mutual support groups, there have been no systematic attempts to
implement and evaluate routine outcome monitoring (ROM) in these settings. Unlike other mutual support groups for addiction,
trained facilitators lead all Self-Management and Recovery Training (SMART Recovery) groups, thereby providing an opportunity
to implement ROM as a routine component of SMART Recovery groups.

**Objective:**

This study protocol aims to describe a stage 1 pilot study designed to explore the feasibility and acceptability of a
novel, purpose-built mobile health (mHealth) ROM and feedback app (Smart Track) in SMART Recovery groups coordinated by SMART Recovery Australia (SRAU) The secondary objectives are to describe Smart Track usage patterns, explore psychometric properties of the ROM items (ie, internal reliability and convergent and divergent validity), and provide preliminary evidence for participant reported outcomes (such as alcohol and other drug use, self-reported recovery, and mental health).

**Methods:**

Participants (n=100) from the SMART Recovery groups across New South Wales, Australia, will be recruited to a nonrandomized, prospective, single-arm trial of the Smart Track app. There are 4 modes of data collection: (1) ROM data collected from group participants via the Smart Track app, (2) data analytics summarizing user interactions with Smart Track, (3) quantitative interview and survey data of group participants (baseline, 2-week follow-up, and 2-month follow-up), and (4) qualitative interviews with group participants (n=20) and facilitators (n=10). Feasibility and acceptability (primary objectives) will be analyzed using descriptive statistics, a cost analysis, and a qualitative evaluation.

**Results:**

At the time of submission, 13 sites (25 groups per week) had agreed to be involved. Funding was awarded on August 14, 2017, and ethics approval was granted on April 26, 2018 (HREC/18/WGONG/34; 2018/099). Enrollment is due to commence in July 2019. Data collection is due to be finalized in October 2019.

**Conclusions:**

To the best of our knowledge, this study is the first to use ROM and tailored feedback within a mutual support group setting for addictive behaviors. Our study design will provide an opportunity to identify the acceptability of a novel mHealth ROM and feedback app within this setting and provide detailed information on what factors promote or hinder ROM usage within this context. This project aims to offer a new tool, should Smart Track prove feasible and acceptable, that service providers, policy makers, and researchers could use in the future to understand the impact of SMART Recovery groups.

**Trial Registration:**

Australian New Zealand Clinical Trials Registry (ANZCTR): ACTRN12619000686101; https://anzctr.org.au/Trial/Registration/TrialReview.aspx?id=377336.

**International Registered Report Identifier (IRRID):**

PRR1-10.2196/15113

## Introduction

### Background

Using standardized outcome measures to regularly monitor client progress in alcohol and other drug (AOD) settings is an important mechanism for monitoring the effectiveness of service provision [1-3]. Routine outcome monitoring (ROM) provides clinicians with timely feedback about client progress and allows clinicians to tailor treatment to the individual needs of clients and guide treatment decisions [4]. This may be of particular importance when a client is *not on track* (ie, not improving in line with clinical norms [4]). ROM has been specifically recommended for use in AOD treatment settings as the provision of tailored feedback to clients has been found to improve treatment outcomes across a range of AOD treatment settings (eg, acute, community, veterans) [3,5,6]. Evidence also supports clinician use of ROM and tailored feedback to enhance outcomes and/or prevent further deterioration for those clients identified as *not on track* early in addiction and/or mental health treatment [7,8].

Despite the importance of ROM and tailored feedback, ongoing variability in the implementation, sustainability, and use of ROM data has been noted [9]. The time associated with the completion, scoring, interpretation, and feedback of outcome assessments represents a key barrier to systematic implementation [6,9]. Using a digital platform to administer ROM and feedback may help address these concerns. Mobile health (mHealth) [10] apps can provide quick, easy, interactive, and engaging platforms for tracking and accessing information about health and health-related behaviors [11]. Evidence from the United Kingdom suggests that almost 60% of individuals who access AOD treatment own a smartphone [12]. This figure is likely higher in Australia as it is the leading global adopter of smartphones (88% ownership [13]). Given the ubiquity of smartphones, smartphone apps have the added benefit of engaging individuals in real time, in their natural environment, and offering moment-to-moment support as needed [14]. Moreover, a key benefit highlighted in a recent systematic review of mHealth apps is their ability to provide timely, individualized feedback [15]. Accordingly, an opportunity exists to utilize mHealth to enhance engagement, streamline administration, and put the client at the center of the ROM and feedback process.

To date, much of the literature on ROM and feedback has focused on the provision and use of feedback by clinicians [16,17]. Improving client involvement in the feedback process represents an important clinical and research priority [18]. It is not only consistent with the principles of recovery-oriented service provision and strengths-based care [19] but is also therapeutically useful. Within mental health settings, the benefits of providing clients with outcome feedback include improved client insight; enhanced knowledge, skill, and confidence to effectively self-manage their condition(s); and greater satisfaction, engagement, and involvement in treatment [16]. Evidence from related approaches (eg, *therapeutic assessment* [20]) has also shown that providing clients with assessment feedback during psychotherapy promotes client self-verification, self-discovery, and self-enhancement [18]. Moreover, delivering feedback directly to the client seems to further enhance the positive impact of ROM on treatment outcome(s), particularly among group-based treatment settings [6]. Therefore, to meet this important need of putting the client at the center of the ROM and feedback process, during the first phase of this study, we developed a purpose-built mHealth app.

### Mutual Support Groups

*Mutual support* refers to the reciprocal provision of social, emotional, and informational support by group members undergoing recovery from addiction [21]. Mutual support groups are widely available [22], commonly accessed [23], and play an extremely important role in the treatment of AOD use disorders [2,24]. Two approaches recommended by clinical guidelines include 12-step models (eg, Alcoholics Anonymous) and Self-Management and Recovery Training (*SMART Recovery* [2,24]). Although the 12-step models are traditionally the most well-known and accessed models for mutual support [22], other approaches (eg, SMART Recovery) are gaining momentum. For example, SMART Recovery Australia has seen an almost 40% increase in groups over the last 4 years, with over 300 groups currently running nationwide [25]. Although accumulating evidence points to the benefit of participating in mutual support groups [26,27], much of the research is derived from the 12-step models. In light of the growth of SMART Recovery groups, expanding the evidence base beyond the 12-step models is a priority. A major limitation in developing a strong evidence base is the lack of outcome data evaluating service delivery. Accordingly, the purpose-built mHealth app developed during the first phase of the study provides a mechanism for not only improving service provision but also providing unique insights into the outcome(s) demonstrated by SMART Recovery participants.

Although many AOD services provided by public health and nongovernment organizations are contracted to monitor client outcomes routinely [28], we are unaware of any research describing the use of ROM in mutual support groups for addictive behaviors. As a trained facilitator leads all SMART Recovery groups, a unique opportunity exists to work with SMART Recovery facilitators to embed ROM and tailored feedback as a standard component of the groups. Investigating the use of ROM and feedback within a mutual support setting helps address the need for improved participant involvement in the assessment and feedback process [18], in addition to building a platform for improving the evidence base for SMART Recovery, a clinical and research priority [27].

### This Study

In this paper, we detail the study protocol for a nonrandomized, prospective, single-arm pilot study, with a concurrent cost evaluation and nested qualitative evaluation designed to explore the feasibility and acceptability of a novel mHealth ROM and feedback app (*Smart Track*) in SMART Recovery groups coordinated by SRAU. The secondary objectives are to describe Smart Track usage patterns, psychometric properties of the ROM items, and participant-reported outcomes.

## Methods

### Approval, Registration, and Reporting

This study was approved by the University of Wollongong and Illawarra Shoalhaven Local Health District (ISLHD) Health and Medical Human Research Ethics Committee (HREC; 2018/099; HREC/18/WGONG/34). The trial has been registered with the Australian New Zealand Clinical Trials Registry (ACTRN12619000686101). Any amendments will be submitted to the ISLHD HREC before implementation, as per HREC guidelines. Any important protocol modifications will be reported in the outcomes paper. To enhance the quality, completeness, and transparency of the proposed study, this study protocol follows the Standard Protocol Items: Recommendations for Interventional Trials [29] and the Consolidated Standards of Reporting Trials-eHealth checklist [30] (Multimedia Appendix 1).

### Participants

#### Eligibility

Participants must be at least 18 years of age, currently participating in one or more SMART Recovery groups located within New South Wales (NSW), have a current email address or be willing to obtain an email address, and be able to comprehend English at a level sufficient to complete study requirements.

Participants will be eligible irrespective of their self-reported computer and/or smartphone literacy. No restrictions will be placed on concomitant care, including the frequency or duration of SMART Recovery group participation or participation in other forms of AOD treatment. Participants will only be excluded if they are unable or unwilling to provide informed consent. Exclusion criteria were kept to a minimum to ensure that the study sample is representative of people attending SMART Recovery groups.

#### Smartphone Ownership

Although we expect that most participants will own a smartphone [12,13], potential participants do not need to own a smartphone to participate. The research team will provide tablets to study sites (locations where regular SMART Recovery groups are held) so that participants can use the tablet before and/or after attending a group to complete the ROM questions and receive feedback.

### Study Setting

Potential participants will be sourced from the SMART Recovery groups held in NSW, Australia. A full list of study sites will be reported in the outcomes paper. SMART Recovery groups are held in the community as well as in inpatient, outpatient, and clinical health organizations, including private, public, and not-for-profit mental health, AOD, and general health services. Online SMART Recovery groups are also available. A detailed description of the SMART Recovery groups has been provided elsewhere [31]. Briefly, SMART Recovery focuses on self-empowerment and utilizes evidence-based techniques (eg, cognitive behavioral therapy and motivational interviewing) [32]. To ensure that our sample adequately reflects SMART Recovery participants, study sites with established SMART Recovery groups were selected to reflect a range of geographical locations and service providers. At the time of manuscript submission, 147 groups were conducted throughout the NSW.

### Enrollment

Group facilitators will use a script to introduce the study to potential participants and invite expressions of interest. The following strategies will be adopted to maximize adequate enrollment. Group facilitators will be asked to check in with participants regarding the completion and/or return of expression of interest forms (across a maximum of 3 meetings). A member of the research team will also visit SMART Recovery groups throughout the recruitment period to directly provide group members with information about the study and collect the expression of interest forms. Depending on accrual, the study may also be advertised (eg, online, local media, flyers/pamphlets, and study website) to extend participant recruitment beyond this study’s sites.

### Informed Consent

A member of the research team ([name]) will collect informed consent from all study participants (written or verbal according to the participant’s preference). A copy of consent (audio recording and/or signed consent form) will be retained for all study participants and securely stored according to the HREC–approved methods.

### Overview of the mHealth Routine Outcome Monitoring and Feedback App (Smart Track)

The Smart Track app was designed for participants attending SMART Recovery groups. ROM items are intended for weekly completion. However, it is up to the individual to decide whether, when, and how they engage with Smart Track. Given the low-risk, low-burden nature of this study, there are no contingencies for discontinuing access to the Smart Track app. Owing to app store regulations, Smart Track will not be restricted to study participants. It will be freely available for download through Android and iPhone Operating System stores (only data from those who provide consent will be included in the study).

Publications detailing the methods and findings from the qualitative work [33] and app development process (including theoretical foundations) will be reported separately. To provide context, a brief summary is presented here. The Smart Track app was developed during the first phase of this study using participatory design workshops and an iterative development process informed by the (1) consideration of existing ROM tools, (2) qualitative feedback [33] and usability testing sessions with SMART Recovery participants and facilitators, (3) clinical and research expertise from the members of the expert advisory and steering committees, and (4) technological and creative expertise of the development team employed to work on this study (GHO, Sydney) [34].

The functionality of Smart Track was initially tested with 3 members of the research team. Several bugs were identified and fixed before the amended beta version was released to a convenience sample (n=40) for further testing. This convenience sample of beta testers included members of the expert advisory committee, steering committee, SMART Recovery board members, and SMART Recovery facilitators. Further refinements were made in line with the feedback received (bug fixes, minor amendments to functionality, and content).

#### Smart Track Routine Outcome Monitoring Domains and Items

Consistent with clinical guidelines [3,35] and informed by recommendations arising from systematic reviews evaluating ROM in both mental health [18] and addiction [6] settings, we sought to create a tool that provided multidimensional assessment and feedback. Utilizing an iterative process, we generated a list of candidate outcomes (group attendance; goal setting and attainment; values; self-efficacy; quality of life; self-care; mental health; quantity, frequency, and impact of addictive behavior(s); social support; financial stability; optimism; and frequency, strength, and duration of urges). Corresponding assessment items and/or instruments were then identified to measure these domains. Where possible, validated free-to-access measurement instruments were selected from the published literature. Some changes to the structure, wording, and/or response format were required to improve the clarity and appropriateness of some items. The final item set included in the tool is detailed in Multimedia Appendix 2 [36-47] as a function of the target domain and assessment frequency.

#### Smart Track Tailored Feedback

The same iterative process was used to inform the content, format, and frequency of the Smart Track feedback. On the basis of the participants’ responses to individual ROM items and/or subscale scores, tailored visual cues (eg, colors and arrows) are used to provide a *snapshot* of progress within each domain (eg, current score range and/or direction of progress). Participants can also select one or more domains to receive further detailed feedback (written and visual).

The written feedback comprises encouraging statements, self-reflection questions, and/or self-management suggestions. As health messages are more effective when they are tailored to the individual [48] and tailored feedback is central to both popularity [49] and effectiveness [14] of mHealth apps for alcohol use, written feedback and visual cues are tailored. Visual feedback comprises a graph illustrating the participant’s progress over time (with the option of viewing data for the week, month, and year). Guided by the literature highlighting the utility of providing feedback according to the level of observed progress (eg, *on-track* or *off-track* [16]) and informed by previous *stop-light*–style ROM feedback systems (see the study by Kendrick et al [7] for a review), written feedback and visual cues are tailored according to three pathways, based on whether individual domain scores suggest (1) a *good* score range or improvement (green), (2) an *ok* score range or stability (yellow), or (3) a *less good* score range or deterioration (red). The chosen logic allows feedback content and visual cues to be tailored such that all progress is encouraged and reinforced, with a specific focus on (1) maintaining change (green), (2) highlighting additional change(s) that may be of benefit (yellow), or (3) troubleshooting difficulties and/or seeking support (red).

#### Additional Features of Smart Track

Inconsistent engagement (client and/or clinician) has long been identified as a challenge to both ROM and feedback [50] and, more broadly, the mHealth literature [51]. Therefore, in addition to the core ROM and feedback functionality, several additional features (Table 1) have been included. Aside from the hints, tips, and motivational statements (which automatically feature once per day that the app is used), it is up to the individual as to how frequently they access various features.

**Table 1 table1:** Additional Smart Track features.

Feature	Description
Customizable support(s) and personal motivation(s)	Participants have the option of tailoring the app content by uploading key contact number(s), support services and/or personal motivation(s) for change (photo, audio, video, and/or written)
Resources	Information about self-management strategies (including SMART^a^ Recovery resources) and motivational stories from people with lived experience of addictive behavior(s)
Hints, tips, and motivational statements	A self-management tip, motivational statement, or inspirational quote will be included as pop-up content. These brief messages comprise direct and adapted quotes from the transcripts of the qualitative interviews
Journal	There is a free text box on each feedback page to allow participants to reflect on their progress and/or the tailored feedback provided
Interactive urge log	In addition to tracking the number, frequency, and strength of urges, when the participant reports an urge, this interactive tool prompts the participants to manage their urges, log triggers, and reflect on how to maintain and/or improve effective urge self-management

^a^SMART: Self-Management and Recovery Training.

#### Implementation Strategies

The app contains an in-built *walk through* to orient new users to the features of the app. We also intend to develop a brief tutorial to assist participants with app download and set up. Consistent with the recommendations for improving ROM uptake [9], SMART Recovery facilitators at each study site will assume the role of *local champions* of Smart Track. The research team will work with the facilitators to orient them to the app so that they are confident in responding to the participants’ questions about ROM completion and troubleshooting any difficulties that may arise. Participants and facilitators may also contact the research team directly for support. SMART Recovery facilitators will also prompt, encourage, and support study participants to regularly complete the ROM questions before and/or attending a SMART Recovery group.

In-app push notifications will also be used to prompt participants to complete the ROM items. In-app notifications (red marker) will also be used to highlight section(s) that require participants’ attention (eg, outstanding 7-day plan).

### Data Collection Procedures

The participant timeline is outlined in Figure 1, and the corresponding schedule of participant assessments is summarized in Table 2. There are 4 main modes of data collection in this study: (1) participant-completed ROM data collected via Smart Track (Multimedia Appendix 1), (2) broader app-generated data analytics summarizing interactions with Smart Track, (3) quantitative baseline and follow-up assessments with study participants, and (4) qualitative interviews with study participants and group facilitators.

Baseline and follow-up assessments will primarily be conducted over the telephone by a member of the research team (a trained clinical psychologist). To promote follow-up, appointments will be scheduled at a time convenient to the participants, with options to accommodate participants’ preferences for video link, face-to-face, and/or self-report (where feasible). Telephone, text, letter, and/or facilitator prompting will be utilized (as needed) to remind the participants of upcoming and/or missed appointments.

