	**Telephone interview**											
	Demographics			✓								✓

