	**Network of Alcohol and other Drug Agencies Client Outcome Management System**											
		Severity of Dependence Scale		✓								✓
		Drug and alcohol use		✓								✓
		Kessler 10+ scale		✓								✓
		The World Health Organization Quality of Life–8		✓								✓
		New South Wales minimum data set items (living arrangements and income)		✓								✓
		BTOM-C^c^ items on arrests		✓								✓
		BTOM-C items on risky drug using practices		✓								✓
	Substance Use Recovery Evaluator			✓								✓
	Client Services Receipt Inventory			✓								✓
	Mobile App Rating Scale–user version									✓		
	Digital Working Alliance Inventory									✓		✓
	Qualitative interview (n=20)											✓

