### Data Handling and Storage

Initially, the ROM data entered by participants into Smart Track will be stored locally on the participants’ phones. When the participants connect to the internet, ROM data will be transmitted to a secure mobile and web app development platform (managed by SRAU), before transmitting to a secure server hosted by the University of Wollongong.

The participants’ responses to the baseline and follow-up research assessment instruments will be entered at the time of interview directly into REDCap, a secure web application for building and managing online surveys and databases. Further information about data management, monitoring, and dissemination is provided in Multimedia Appendix 3.

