##### Nested Qualitative Evaluation

Qualitative interviews will be conducted 2 months postbaseline to explore the experience and opinions of participants with diverse engagement with Smart Track. Participants will be purposively sampled according to their baseline characteristics, pattern of Smart Track usage, and responses to the 2-month follow-up assessment. Specifically, we wish to explore the experience and opinions of 2 groups of SMART Recovery participants: (1) those who attended SMART groups regularly and completed the ROM regularly (n=10) and (2) those who attended SMART groups regularly and did not complete the ROM regularly (n=10). A qualitative researcher independent from the research team will use a topic guide to ask additional open-ended questions to the selection of participants (n=20) until the nominated sample size in both groups is reached. The research team will monitor recruitment to ensure that there is an adequate distribution of gender, main behavior of concern, geographical location, and group setting. Two corresponding groups of SMART Recovery facilitators (n=5 for each group) will also be recruited, namely (1) one group with members who regularly used Smart Track and (2) another group with members who did not regularly use Smart Track.

All interviews will be audio-recorded. A professional transcriber working under a confidentiality agreement will transcribe the recordings. The transcripts will be checked against the recordings for accuracy and deidentified (by removal of identifying information).

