### Study Outcomes

Primary and secondary endpoints are presented in Tables 3 and 4, respectively.

**Table 3 table3:** Primary endpoints.

Primary objective	Primary endpoint
To explore the feasibility of using Smart Track as part of SMART^a^ Recovery groups for the purposes of ROM^b^ and tailored feedback	Proportion of eligible participants who consent to the study Proportion of missing data for each of the ROM items/instruments at each week of administration, across the 2-month period of Smart Track usage Costs associated with developing Smart Track and maintaining the app until the completion of data collection Participant engagement with Smart Track, as indexed by data analytics captured daily across the data collection period
To explore the acceptability of using Smart Track as part of SMART Recovery groups for the purposes of ROM and tailored feedback	Detailed qualitative feedback from SMART Recovery group members and facilitators to explore their experience of and satisfaction with Smart Track (2-month follow-up) Quality ratings as assessed by participant and facilitator ratings of the user version of the Mobile App Rating Scale (2-week follow-up) and Mobile App Rating Scale (2-month follow-up), respectively Digital therapeutic alliance ratings as assessed by participant ratings of the Digital Working Alliance Inventory (2-week and 2-month follow-up)

^a^SMART: Self-Management and Recovery Training.

^b^ROM: routine outcome monitoring.

**Table 4 table4:** Secondary endpoints.

Secondary objective	Secondary endpoints
To explore how participants engage with the app and describe usage patterns	Demographic, clinical, and treatment factors (as measured by Client Service Receipt Inventory, COMS^a^, and SURE^b^ at baseline and 2-month follow-up) associated with (in)completion of Smart Track ROM^c^ items Data analytics captured daily across the data collection period
To provide preliminary evidence for the psychometric properties of the ROM items administered by Smart Track	Internal reliability and convergent and divergent validity of COMS and SURE items administered by Smart Track (relative to the complete versions administered at baseline and 2-month follow-up)

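### By default, participants give the uMARS and D-WAI ratings by telephone to a member of the research team that led the app's development and supports its users; self-completion first would reduce courtesy bias

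*Protocol article*

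**What the plan says.** Data Collection Procedures sets the default mode and assessor: "Baseline and follow-up assessments will primarily be conducted over the telephone by a member of the research team (a trained clinical psychologist"). Participants may instead ask for "video link, face-to-face, and/or self-report (where feasible"), so self-report is an accommodation and not the rule.

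In Table 2, the heading "Telephone interview" stands above the participant row "Mobile App Rating Scale–user version" (2-week follow-up) and the Digital Working Alliance Inventory row (2-week and 2-month follow-up). Data Handling and Storage says that responses to the baseline and follow-up instruments "will be entered at the time of interview directly into REDCap".

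Table 3 under Study Outcomes lists three acceptability endpoints. One is qualitative feedback. The second begins "Quality ratings as assessed by participant and facilitator ratings of the user version of the Mobile App Rating Scale". The third is the D-WAI rating. The Statistical Analysis section summarises the uMARS and D-WAI ratings descriptively.

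The Background says that the authors developed the app in the first phase of the study. Implementation Strategies makes the research team a direct support contact for users.

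For the qualitative interviews the article states a separation: "A qualitative researcher independent from the research team will use a topic guide". It states none for the uMARS or D-WAI.

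**The concern.** People tend to be kinder about a product when they score it to someone connected with it. Under the default procedure, the participant gives the scores by telephone to a member of the team behind the app, and that person records them. The expected direction of any bias is upward.

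The design has no means of absorbing such a bias. There is one arm, so no comparator in which a shift would cancel. Participants rate the uMARS once, so no later participant uMARS could reveal inflation. A confidence interval reflects sampling error only and would not widen to show the shift.

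The article separates interviewer from team for one acceptability endpoint and states no such separation for the other two. Mode is also left to participant preference, so spoken and self-completed ratings may be pooled.

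**Working it through.** The point concerns mode and assessor. The plan gives no figure for it, so the main check sets the sections side by side.

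1. *Which endpoints.* Table 3 has three acceptability endpoints; the uMARS and D-WAI are two of them.
2. *Which mode.* Table 2 puts both participant rows in the telephone block. Data Collection Procedures makes the telephone the main mode, and Data Handling and Storage has answers entered during the interview. The three sections agree.
3. *Which assessor.* The Table 2 heading alone does not settle this, because the qualitative interview sits in the same block and is assigned to an independent researcher. The assessor comes from Data Collection Procedures, which names a research-team member for follow-up assessments. No exception is stated for the uMARS or D-WAI.
4. *Relation to the app.* The team led development (Background) and supports users (Implementation Strategies).
5. *Is an alternative at hand?* Eligibility requires participants to "have a current email address or be willing to obtain an email address". Data Handling and Storage describes REDCap as a tool for online surveys. Smartphone Ownership provides tablets at study sites. The uMARS is described as an end-user version of the scale.

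*Illustration of size, on assumed values only.* The target of 100 raters comes from the Power section and assumes that everyone responds. The SD (0.5 to 0.8) and the courtesy shift d (0.1 to 0.5 points on a 1-5 uMARS mean) are assumptions.

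- 95% half-width = 1.96 × SD / √100. SD 0.5 gives 0.098; SD 0.8 gives 0.157.
- Smallest ratio of shift to half-width: 0.1 / 0.157 = 0.64.
- Largest ratio: 0.5 / 0.098 = 5.1.
- If a share s self-completes without bias, the pooled shift is d × (1 − s). With d = 0.3, s = 25% gives 0.225 and s = 50% gives 0.15.

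The shift could therefore be smaller than the sampling error or several times larger. The last line shows only that moving part of the sample to self-completion shrinks the pooled bias in proportion. The D-WAI is not illustrated because the article does not give its response range.

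**The case against.** The strongest reply has five parts.

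- *The telephone is not universal.* A reader might infer that every participant speaks the ratings aloud. The text says that assessments are primarily by telephone and allows self-report. The Abstract mentions interview and survey data, the 2-week contact contains only these two instruments, and Figure 1 and the appendices are not shown. Some planned self-completion cannot be excluded. This stands, and the point is therefore about the default.
- *The interviewer is not shown to be conflicted personally.* A reader might infer that participants score the app to its owners or builders. No section says who owns it. An employed development team worked on it, SMART Recovery Australia manages the platform that first receives the ROM data, and the interviewer is described only as a team member and clinical psychologist. What remains is team affiliation.
- *No decision hangs on a score.* A reader might infer that the finding of acceptability rests on the absolute rating. No threshold is stated, the ratings are descriptive, and the independent qualitative interviews deliberately include 10 people who did not complete the ROM regularly. Negative views have a protected route. This limits the damage but does not protect the scores themselves.
- *The size is assumed.* This is correct; the illustration is not evidence that the bias is large.
- *Self-completion has costs.* Participants are eligible whatever their computer literacy, the voucher covers only baseline and 2 months, and scheduled calls are there to promote follow-up. With a link first, those who end up on the telephone will tend to be the less engaged, so comparing modes cannot isolate courtesy bias. All of this stands. It argues for keeping the call as fallback and for reading the by-mode results with care. The missing 2-week voucher applies equally to the 2-week call.

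**Conclusion.** The point holds as a modest design improvement. By default, two of the three primary acceptability endpoints are rated by telephone to a member of the team that led the app's development and supports its users, with no stated separation between rater and team. In a single-arm study with descriptive ratings, any courtesy bias goes straight into the reported scores.

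Its size is unknown and cannot be obtained from the documents; the range of about 0.6 to 5 half-widths rests wholly on assumed SDs and shifts and on full response. The article does not contradict itself here, and the study remains viable as written. The conclusion assumes that the full protocol does not already make these two instruments self-completed.

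**What to change.** Make self-completion the default for the participant uMARS (2 weeks) and D-WAI (2 weeks and 2 months). Email a REDCap survey link ahead of the scheduled call, or offer the on-site tablet to those without a smartphone. Tell participants that the interviewer will not see their answers, and set REDCap access so that the interviewer sees only whether the form is complete. Keep the scheduled call as fallback for those who have not completed it. The COMS, SURE and CSRI can stay as interviews.

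Add one field for completion mode and report the ratings overall and by mode. State that mode is confounded with engagement, so the by-mode comparison is descriptive and does not measure courtesy bias.

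The cost is one REDCap survey form, one extra field and a change of wording; the platform and the email requirement are already in place. The downside is some late or missing forms, and residual bias among those still rated by telephone.
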